## **2.3 Study design**

This study is a Swiss monocentric non-randomised qualitative study.

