# 1 BACKGROUND AND RATIONALE

Recent data brings out that the CS rate in Switzerland is quite high, reaching 33.4 % (8). Though, the reasons to this increasing amount of CS are not fully known. Therefore, it is absolutely necessary to expand the existing knowledge in different fields, including the biomechanics of childbirth. Numerous CS are performed in response to an obstructed labour, especially when the foetus does not engage in the pelvis near full dilatation. In order to manage such situations, midwives currently position parturients in pragmatic postures. Although not verified by data, this care management suggests that it is possible to impact the position of the bone segments at stake for vaginal birth including pelvis and lumbar spine and to promote the descent of the foetus through the pelvic inlet plane. In his PhD thesis about vaginal birth biomechanics, [name] et al investigated this area and found out that an optimized position similar to the squatting position (hyperflexion of the thighs and loss of the lumbar lordosis) could be close to the perfect delivery position in terms of ability for the foetus to go through the pelvic inlet plane (9). Although these findings are encouraging, it is yet to be confirmed in clinical practice, particularly when a dystocia occurs (10). Prior to doing that, it is though necessary to validate the optimized posture in terms of acceptability in a qualitative clinical study. In this study, fifteen to twenty parturients who respond to the inclusion criteria and whose foetus does not engage in the pelvis near full dilation will be asked to adopt the optimized position for a twenty minutes period. The investigator will then consign information reflecting the progress of the labour on a data sheet. As during labour midwives already position parturients in various postures, some of which very similar to the suggested optimized position, it is sensible to place the study in the risk A category according to ClinO, Art. 61.

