### 2.2 Primary and secondary endpoints

In order to test the hypothesis, the primary endpoint will be whether or not the participants manage to maintain the optimized birthing position for the twenty minutes duration of the study, and if they do, how well they manage it. Some variables like age, parity or history of difficult delivery will be described for each participant. In complement to the primary endpoint, the number of parturients who will refuse to participate to the study will give additional insight into the acceptability of the optimized birthing position. If the reason of their refusal is mentioned, it will then be used to give an additional insight into the acceptability of the optimized birthing position.

The secondary endpoint variables will include:

- General information
- Risk factors of non-engagement of the foetus at full dilation
- Foetal parameters
- Delivery outcome

- Adverse events
- Presence of symphyseal separation

However, this study was not design to obtain significant results regarding the secondary endpoint variables.

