## **2.4 Study intervention**

The intervention will consist in positioning the parturient in an optimized position. It means the parturient will be asked to adopt a supine position with a hyperflexion of the thighs and a flat back, and to maintain the position for twenty minutes. This period of time represents approximately twenty uterine contractions and will give the opportunity to appreciate the effectiveness of the measure without being to constraining for the participants. Most of the time, the patients indeed have epidural anaesthesia and it is though not recommended to make them adopt a position for a prolonged amount of time, in order to avoid any risk of malposition or nerve compression. Help from the investigator or the midwife in charge will be provided if needed or requested. The labour will continue during the twenty minutes period, as obstetrical labour once started can't be interrupted.

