## **4 STATISTICS AND METHODOLOGY**

### **4.1. Statistical analysis plan and sample size calculation**

In this observational pilot study, no sample size was defined.

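### Giving up and discomfort are what the study tests, yet the protocol does not plan to record or use why women who tried the position stopped

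*Protocol*

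**What the plan says.** Section 1 gives the purpose: "it is though necessary to validate the optimized posture in terms of acceptability in a qualitative clinical study". Section 2.3 repeats the label: "This study is a Swiss monocentric non-randomised qualitative study". Section 2.1 defines acceptable and feasible as being able to keep the position for some time without abandoning it or being uncomfortable, and says acceptance will be judged with a satisfaction scale.

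The primary endpoint in 2.2 has two parts. The first is "whether or not the participants manage to maintain the optimized birthing position for the twenty minutes duration of the study"; the second is "and if they do, how well they manage it". On women who decline, 2.2 says "If the reason of their refusal is mentioned, it will then be used to give an additional insight".

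Section 3.4 lists four grounds for withdrawal: withdrawn consent, disease progression, foetal heart rhythm disorder and progress of labour. It adds that the data available at withdrawal are kept and used. Section 4.2 says drop-outs are replaced, their data are handled like the rest, and their number counts towards acceptability. On what is written down after the hold, section 1 says "The investigator will then consign information reflecting the progress of the labour on a data sheet".

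On study type, section 2.4 says "The intervention will consist in positioning the parturient in an optimized position", while 4.1 says "In this observational pilot study, no sample size was defined".

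**The concern.** A study of whether a posture is accepted learns most from the women who tried it and could not, or would not, go on. They are the group for whom the protocol plans least. A woman who refuses may have her reason used, although she never held the position. A woman who completes has her experience graded. A woman who starts and stops contributes to a count.

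That count is ambiguous. A stop because the foetal heart rhythm changed, or because labour moved on, says nothing about whether the woman tolerated the posture. A stop because of pain, discomfort or fatigue is exactly the failure named in the hypothesis. If both enter one number, the acceptability result can be too pessimistic, and a reader cannot tell by how much. The woman's own reason cannot be recovered at the analysis stage if nobody asked for it, so a separate analysis plan would not repair this.

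**Working it through.** The protocol states no sample size calculation, error rate or target, so there is no figure to reproduce. The check sets the sections side by side by group of women.

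| Group | Tried the position? | Experience graded? | Reason planned for use? | Stated role |
|---|---|---|---|---|
| Refuse (2.2) | No | No | Yes, if volunteered | Number and reason |
| Start and stop (3.4, 4.2) | Yes | Not under 2.2 | Not stated | Number; available data kept |
| Complete (2.2) | Yes | Yes | Not stated | Primary endpoint, both parts |

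1. *Refusers have no experience of the posture.* Under 3.2, written consent is sought at the antenatal consultation and confirmed orally on admission to the labour ward. Both precede positioning.
2. *Grading is conditional on completion.* The second part of the endpoint applies only if the first part is met.
3. *The withdrawal list does not isolate intolerance.* Two of the four grounds in 3.4 (foetal rhythm disorder, labour progression) are not intolerance. None of the four is discomfort or inability to hold the position. A woman who gives up for that reason is either filed under withdrawn consent or fits no category.
4. *The count mixes causes.* Section 4.2 takes the number of drop-outs as evidence on acceptability and does not exclude stops made for foetal or labour reasons.
5. *Size per woman.* Section 3.1 plans twenty women and section 1 fifteen to twenty. One stop is 1/20 = 5% or 1/15 = 6.7% of the women positioned, before any replacements.
6. *Illustration.* The protocol gives no expected drop-out rate, so assume that 8 of 20 women stop. Then 12/20 = 60% held the position and 8/20 = 40% did not. From the count alone, the proportion stopping for intolerance could lie anywhere from 0/20 = 0% to 8/20 = 40%. Withdrawal grounds recovered from retained data would narrow this range.

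On the label, 2.4 assigns the posture to the woman, and 5.2 requires events to be assessed for causality against the trial intervention. A study that does this is not observational. The data described are completion, how well it was managed, and a scale. No interview or other qualitative method is described.

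**The case against.** The best defence is that the plan holds more than a bare count, and much of it stands.

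- The endpoint is not just yes/no. It has a graded part, and the satisfaction scale in 2.1 is reported by the woman and not expressly limited to completers.
- Section 3.4 names causes of withdrawal and keeps the data, and adverse events are a secondary endpoint. Some stops for foetal or labour reasons could therefore be told apart from intolerance.
- Section 7.2 sends all necessary data to paper case report forms that are not shown. A field for the reason may exist. Section 1 says the data sheet reflects labour progress, but not that it holds nothing else.
- The protocol asks whether the position is accepted, not which element of it fails. Section 6.1 places the formal definition of the position in a separate project.

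A reader might therefore infer that the study cannot explain any failure, or that no reason would be available for any woman who stops. The documents do not support either reading.

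A reader might also infer that the design labels exclude one another. They do not: *qualitative* describes the kind of data and *interventional* describes assignment, so a study can be both. Only *observational* conflicts with 2.4. Nor does that word leave the absence of a sample size without a ground, since the same sentence calls the study a pilot and that is reason enough for no formal calculation.

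What the defence does not supply is any statement that women who stop will be asked why, or that stops will be separated by cause when acceptability is judged.

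**Conclusion.** The point holds in a limited form and should be acted on before recruitment. The hypothesis is about giving up and discomfort. The protocol grades experience only in completers, plans to use reasons only from refusers, and counts drop-outs without separating intolerance from foetal or labour causes. Every woman positioned is affected, and the loss is greatest for those who stop.

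This rests on two assumptions: that the unseen case report form has no field for the reason for stopping, and that at least some women stop. If such a field exists, what remains is to say so in the protocol and to say how it will be used.

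The wording of 4.1 is a minor matter. Correcting it changes no result and does not alter the position on sample size.

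**What to change.** In 2.2 and 4.2, state that every woman positioned, whether or not she completes and including those later replaced, is asked for the following as soon as feasible after the position ends:

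- the satisfaction scale;
- one coded question on the main reason for stopping or, in completers, the main discomfort;
- one open question.

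Tabulate the answers with the primary result, over all women positioned, with stops for intolerance shown apart from stops for foetal or labour reasons. The codes should allow that separation, because the grounds in 3.4 alone do not.

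Use one design label in sections 1, 2.3 and 4.1, for example *single-arm interventional pilot of feasibility and acceptability*.

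The cost is a few sentences of protocol text and two questions on the case report form, estimated at about two minutes per woman. The downside is a small extra burden in labour.

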## **2.4 Study intervention**

The intervention will consist in positioning the parturient in an optimized position. It means the parturient will be asked to adopt a supine position with a hyperflexion of the thighs and a flat back, and to maintain the position for twenty minutes. This period of time represents approximately twenty uterine contractions and will give the opportunity to appreciate the effectiveness of the measure without being to constraining for the participants. Most of the time, the patients indeed have epidural anaesthesia and it is though not recommended to make them adopt a position for a prolonged amount of time, in order to avoid any risk of malposition or nerve compression. Help from the investigator or the midwife in charge will be provided if needed or requested. The labour will continue during the twenty minutes period, as obstetrical labour once started can't be interrupted.

# **3 STUDY POPULATION AND STUDY PROCEDURES**

## **3.1 Inclusion and exclusion criteria, justification of study population**

The study population will be constituted of twenty parturients with interrupted labour due to the non-engagement of the foetus in the pelvis at full dilation. Only the parturients responding to the inclusion criteria will participate to the study.

Study inclusion criteria:

- Informed consent as documented by signature
- Parturient in situation of mechanical dystocia (non engagement at full dilation)

Study exclusion criteria:

- Inability or medical contraindications to undergo the investigated intervention (e.g. orthopaedic injury or disease preventing the parturient from adopting the optimised position)
- Clinically significant concomitant diseases
- Incapacity of judgment
- Inability to follow the procedures of the study due to language problems, psychological disorders, dementia, etc.
- Foetus cardiac rhythm disorder

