## 2 STUDY OBJECTIVES AND DESIGN

### 2.1 Hypothesis and primary objective

The hypothesis is that the optimized birthing position, as described in the first chapter of this protocol, is an acceptable and feasible position. This means that the included parturients will be able to maintain the optimized birthing position for a certain amount of time without giving up or feeling uncomfortable achieving it. The primary objective of the study is thus to determine, by clinically testing the optimized position on a reduced sample of parturients, if it is well accepted by them with a satisfaction scale.

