### **4.2. Handling of missing data and drop-outs**

Dropouts will be replaced by recruitment of subsequent new subjects. The data of the participants dropping out from the study before the end of the twenty minutes period will be handled and archived the same as the remaining data. The number of drop-outs will indeed contribute to assess the acceptability of the position.

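### Section 3.1 lists inability to undergo the position as an exclusion, although that ability is the primary endpoint, so a failed attempt can be read as an ineligible case or as a failure

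*Protocol*

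**What the plan says.** The exclusion list in Section 3.1 of the protocol begins with "Inability or medical contraindications to undergo the investigated intervention (e.g. orthopaedic injury or disease preventing the parturient from adopting the optimised position". Inability stands beside medical contraindication as a separate ground, and the orthopaedic case is given only as an example.

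Section 2.1 hypothesises that the position "is an acceptable and feasible position" and explains this as meaning that "the included parturients will be able to maintain the optimized birthing position for a certain amount of time without giving up or feeling uncomfortable". The primary endpoint in Section 2.2 is "whether or not the participants manage to maintain the optimized birthing position for the twenty minutes duration of the study". Section 2.4 describes the intervention: "the parturient will be asked to adopt a supine position with a hyperflexion of the thighs and a flat back", and she is then to keep it for twenty minutes, with help if she needs or requests it.

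Two kinds of non-completion are expressly kept as evidence. Section 2.2 uses the number of refusals. Section 4.2 keeps the data of women who stop before twenty minutes and says that "The number of drop-outs will indeed contribute to assess the acceptability of the position". The protocol provides no count of women excluded for inability.

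**The concern.** An eligibility criterion should not turn on the quantity that the trial measures. Take a consented woman with dystocia who is asked to take up the position and cannot reach it. By Section 2.2 she has not maintained it. By Section 3.1 she can also be described as unable to undergo the intervention, and so as not eligible. The protocol does not say which description applies.

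The choice affects the result in one direction only. Classifying such a woman as ineligible removes a failure from the denominator and never a success. With about twenty participants, a few cases handled this way would visibly change the feasibility result, and a reader of the report could not see that it had happened.

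**Working it through.** **Reading the sections together**

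1. *Do exclusion and endpoint describe the same thing?* By Section 2.4 the intervention is adopting the position and keeping it for twenty minutes. Inability to undergo the intervention is therefore inability to adopt or keep the position, and keeping it is the endpoint in 2.2. They overlap.
2. *When is inability judged?* The protocol does not say. The inclusion criterion "Parturient in situation of mechanical dystocia (non engagement at full dilation" can be met only in labour, so eligibility cannot be complete before then. Signed consent comes earlier, at the antenatal consultation (Section 3.2). Inability could be judged at either time.
3. *Is a woman excluded for inability counted elsewhere?*
   - Refusals (2.2): no, because she agreed to take part.
   - Drop-outs (4.2): only if she is first treated as a participant. If she is excluded, no.
   - Withdrawals (3.4): the grounds are withdrawn consent, disease progression, foetal heart rhythm disorder and labour progression. Inability to adopt the position is not among them.

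If she is classed as excluded, no stated tally holds her. If she is classed as a participant, 4.2 does.

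**Illustration of size**

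The plan states no success rate, threshold or inability rate, so there is no figure to reproduce. The only input from the documents is the number of women: twenty in Section 3.1, fifteen to twenty in Section 1. The success count s and the number k excluded after a failed attempt are assumptions.

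- Reported proportion: s/n
- Proportion with the k women counted as not maintained: s/(n + k)
- Overstatement: s/n − s/(n + k) = (s/n) × k/(n + k), which is never negative

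With n = 20 and s = 18 (exact Clopper-Pearson 95% intervals):

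| k | Proportion | 95% CI | Overstatement (points) |
|---|---|---|---|
| 0 | 18/20 = 90.0% | 68–99% | – |
| 1 | 18/21 = 85.7% | 64–97% | 4.3 |
| 2 | 18/22 = 81.8% | 60–95% | 8.2 |
| 3 | 18/23 = 78.3% | 56–93% | 11.7 |
| 5 | 18/25 = 72.0% | 51–88% | 18.0 |

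Other assumed starting points behave alike. From 20/20 = 100%, k = 1, 3 and 5 give 20/21 = 95.2%, 20/23 = 87.0% and 20/25 = 80.0%. From 14/15 = 93.3%, they give 14/16 = 87.5%, 14/18 = 77.8% and 14/20 = 70.0%.

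**The case against.** The strongest reply is that the protocol already handles the case. Being asked to adopt the position is the start of the intervention in 2.4, so a woman who is asked and fails has become a participant and falls under 4.2. The one example in the exclusion is an orthopaedic condition that could be known beforehand, and the other inability criterion in 3.1 (language, psychological disorders, dementia) also describes standing conditions. The hypothesis is worded for included women, and acceptability among women able to undergo the intervention is a coherent target. The study is a small qualitative pilot without a success threshold.

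Much of this stands. Four stronger readings that a reader might infer are not supported:

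- *That such women appear in no count.* This holds only if they are classed as excluded; 4.2 can be read to include them.
- *That staff apply the criterion at the bedside just before positioning.* The protocol gives no time or person for this judgement. Only the dystocia criterion has to wait for full dilation.
- *That 86%, 78% or 72% would be the true rates.* They follow from assumed counts.
- *That excluding women who cannot safely take the position is a flaw.* Excluding medical contraindications is legitimate, and such women are not failures of the endpoint.

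The reply does not remove the ambiguity. The example does not limit the ground, inability is listed separately, and nothing says that a failed attempt cannot be used to invoke it. The study's qualitative character does not settle the matter either, because its primary endpoint is whether women manage the position.

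**Conclusion.** The concern holds as an ambiguity in the primary denominator. The text permits two classifications of a woman who tries and cannot reach the position, and one of them removes only failures. Whether the bias arises, and how large it is, depends on how investigators read the criterion and on how many such women there are; the documents settle neither. Under an assumed 18 of 20 successes, 1 to 5 women classed as excluded would mean an overstatement of about 4 to 18 percentage points. No stated decision threshold would be crossed, but the proportion is the main quantitative evidence for feasibility, and Section 6.1 presents the study as a first step toward using such a position in obstructed labour. The protocol should be changed, because an analysis plan cannot recover women who were never enrolled or recorded.

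**What to change.** - **Section 3.1:** reword so that inability shown only by a failed attempt at the position is not a ground for exclusion. Leave exclusion for medical contraindications unchanged, whenever they are recognised, including those first noticed in labour.
- **Section 2.2:** state that every consented, eligible woman in whom positioning is attempted belongs to the primary denominator, and that failure to reach the position counts as not maintained.
- **Reporting:** give the number of consented women with dystocia excluded under this criterion, with the reasons, alongside the refusals that 2.2 already counts.

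The change concerns classification and does not require positioning anyone who would otherwise not be positioned. It costs a short wording amendment, one CRF line and possibly a lower reported success rate.

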## **3.2 Recruitment, screening and informed consent procedure**

The recruitment of the participants will begin by information during the antenatal consultation in the CHUV polyclinic of gynaecology and obstetrics. The patients will receive the participant information sheet and oral information from the physician in charge or from the co-investigator accompanied by a physician. If they are willing to participate to the study, they will have to sign

the consent form directly at the end of the consultation.

The physician or the co-investigator will explain to each patient the nature of the study, its purpose, the procedures involved, the expected duration, the potential risks and benefits and any discomfort it may entail. Each participant will be informed that the participation in the study is voluntary and that she may withdraw from the study at any time and that withdrawal of consent will not affect her subsequent medical assistance and treatment, or the medical assistance of the foetus.

The participant will be informed that authorised individuals other than their treating physician, including the project leader ([name]), her research assistant ([name]) and the co-investigator ([name]), may examine her medical records.

All participants for the study will be provided a participant information sheet and a consent form describing the study and providing sufficient information for participant to make an informed decision about their participation in the study. A frame of twenty minutes will be given to the parturient in order to decide whether or not she will participate to the study.

The consent form will be signed and dated by the participant and a physician. All the consent forms will be signed during the consultation preceding the admission in the labour ward. A copy of the signed informed consent will be given to each study participant. The consent form will be retained as part of the study records. The informed consent process will be documented in the patient file and any discrepancy to the process described in the protocol will be explained.

At the admission in the labour ward, an oral confirmation of the informed consent will be asked in presence of the co-investigator and the midwife to make sure the parturient still wants to participate to the study.

